## Abstract

**Background:**

Evidence from the USA suggests that the home-based Family Nurse Partnership program (FNP), extending from early pregnancy until infants are 24 months, can reduce the risk of child abuse and neglect throughout childhood. FNP is now widely available in the UK. A new variant, Group Family Nurse Partnership (gFNP) offers similar content but in a group context and for a shorter time, until infants are 12 months old. Each group comprises 8 to 12 women with similar expected delivery dates and their partners. Its implementation has been established but there is no evidence of its effectiveness.

**Methods/Design:**

The study comprises a multi-site randomized controlled trial designed to identify the benefits of gFNP compared to standard care. Participants (not eligible for FNP) must be either aged < 20 years at their last menstrual period (LMP) with one or more previous live births, or aged 20 to 24 at LMP with low educational qualifications and no previous live births. ‘Low educational qualifications’ is defined as not having both Maths and English Language GCSE at grade C or higher or, if they have both, no more than four in total at grade C or higher. Exclusions are: under 20 years and previously received home-based FNP and, in either age group, severe psychotic mental illness or not able to communicate in English. Consenting women are randomly allocated (minimized by site and maternal age group) when between 10 and 16 weeks pregnant to either to the 44 session gFNP program or to standard care after the collection of baseline information. Researchers are blind to group assignment.

The primary outcomes at 12 months are child abuse potential based on the revised Adult-Adolescent Parenting Inventory and parent/infant interaction coded using the CARE Index based on a video-taped interaction. Secondary outcomes are maternal depression, parenting stress, health related quality of life, social support, and use of services.

**Discussion:**

This is the first study of the effectiveness of gFNP in the UK. Results should inform decision-making about its delivery alongside universal services, potentially enabling a wider range of families to benefit from the FNP curriculum and approach to supporting parenting.

**Trial registration:**

ISRCTN78814904.

## Background

Recent estimates show that suboptimal parenting of infants is a major public health issue. As of 31 March 2012, infants (children aged up to one year) accounted for 13% of those who were subject to a child protection plan in England [1]. The most common initial category of abuse for infants was neglect (49%) followed by emotional abuse (22%) and physical abuse (16%). Infants also face four times the average risk of homicide, perpetrators being parents in most cases [2]. Non-accidental head injuries are high resulting in up to 30% mortality and significant neurological impairment for survivors [3]. Furthermore, abuse of very young children may be up to 25% higher than indicated by official estimates [4]. In addition to preventing childhood injury and abuse, sensitive caregiving during the first year is important for promoting optimal child outcomes because brain development then is rapid and vulnerable to negative influences [5]. Trauma and adverse parent–child interactions in infancy elevate cortisol, a strong indicator of stress, and can lead to attachment difficulties, hyperactivity, anxiety and impulsive behavior [6,7].

Overall, evidence concerning the effectiveness of home visiting programs in reducing child maltreatment is inconclusive [8] but the Nurse Family Partnership (NFP) was one of nine home visiting programs identified by the United States Department of Health and Human Services (HHS) as part of their Home Visiting Evidence of Effectiveness (HomVEE) review. The NFP was found to be effective in both decreasing child maltreatment and improving parenting practices [9]. Long-term follow-up of the FNP suggests a 48% reduction in cases of child abuse and neglect by age 15 [10].

The NFP curriculum has strong theoretical underpinnings, both in terms of risk and protective factors, and the mechanisms through which change may be produced [11], drawing on ecological [12], self-efficacy [13] and attachment [14] theories. Ecological theory emphasizes the importance of interactions between the characteristics of individuals and their contexts; self-efficacy theory focuses on an individual’s beliefs that they can successfully carry out behavior required for good outcomes; and attachment theory highlights the importance of the early interactions with the primary caregiver in terms of the child’s later capacity for affect regulation. The cornerstone of the NFP model is the therapeutic nurse-client relationship. Beneficial outcomes found in the US trials include improved prenatal health, fewer childhood injuries, fewer subsequent pregnancies, increased intervals between births, increased maternal employment and improved school readiness [10,15-18]; it has also been shown to have the potential to be cost effective [19]. Results from the US trials of NFP found that it was particularly beneficial for women with ‘low psychological resources’, namely a combination of lower intelligence, mental health problems and low self-efficacy [20]. NFP is now being offered in England, where it is known as the Family Nurse Partnership (FNP), and has been successfully implemented across a range of settings [21-23]. It is currently available in more than 50 locations with further expansion planned [24]. There are, however, mothers-to-be who might benefit from the FNP program but who are not eligible because they are teenage and already had a previous live birth or are over the age of 19 [25]. Group FNP (gFNP) was designed as a program that could be offered to woman not eligible for FNP.

### Group Family Nurse Partnership

Group FNP was developed in 2009, jointly by the UK FNP National Unit and the US NFP National Office led by [name], as a way to use the expertise of the FNP nurses and the learning from the FNP to reach women whose children were at risk of poor outcomes but offered in a different context and to those not eligible for FNP. The newly developed program has the same theoretical basis as the home-based program but is delivered in a local children’s center (or similar community location). The aims of the gFNP program are to improve birth outcomes, develop a warm and authoritative parenting style underpinned by good attachment and knowledge of babies’ developmental needs, promote effective local support networks through contact with other parents, increase take-up of local services, and greater parental self-efficacy to make positive life choices and plan for their future through, for example, thinking about gaining educational qualifications or training for employment. While FNP continues until infants are 24 months old gFNP runs until infants are 12 months of age [26].

The sites delivering gFNP are established FNP sites and gFNP will be delivered in addition to the one to one FNP program in those sites, to clients who would are ineligible for FNP. The program is delivered to each group by two family nurses trained according to US NFP guidelines and who are experienced in delivering home-based FNP [26], one of whom is a practising midwife. Each group comprises between 8 and 12 women, whose partners are encouraged to attend. Women using group based antenatal care such as the Centering Pregnancy Model [27], reported a preference for this approach over traditional care [28-30]. Centering Pregnancy has been associated with improved prenatal outcomes such as reductions in preterm births among high-risk women [31,32]. Following this model of delivery, gFNP provides routine midwifery care in pregnancy and infant health checks according to NICE guidelines [33] during the gFNP session with encouragement for mothers to conduct the necessary pregnancy checks themselves with guidance from the family nurses and midwives. Any out-of-hours antenatal care is managed according to local arrangements (this may involve a community midwifery team or hospital) and intrapartum care is managed by the hospital/birth center midwifery team. The group context should help mothers to develop social networks with other local mothers [34], and to benefit from peer-group learning. Also, meeting in Children’s Centers helps families to become familiar with the other services and to develop regular contact with other professionals when additional support is called for [35].

An implementation evaluation in England found that both the mode of delivery and materials were acceptable to clients and nurses [34-36]. In addition to developing relationships with the family nurses, clients have developed close relationships with group members and made regular use of other services in the Children’s Centers. The delivered content of gFNP is consistent with NFP US National Office recommendations [36] and the prediction is that gFNP is likely to be associated with the same kinds of benefits as the individually delivered program. However, in order to provide optimal information for service providers and commissioners, and to provide the most effective support for potentially vulnerable families, it is important that programs be subject to rigorous randomized trials to provide evidence about efficacy and cost-effectiveness.

### Aims of the study

The main objective of this study is to evaluate whether provision of the Group Family Nurse Partnership (gFNP) program, compared to routine antenatal and postnatal services, can enhance parenting and reduce risk factors for maltreatment in expectant mothers aged < 20 with one or more previous live births or expectant mothers aged 20 to 24 with low/no educational qualifications and no previous live births.

Secondary objectives are to determine whether provision of gFNP will enhance maternal physical and mental health in pregnancy and the experience of pregnancy and delivery for mothers and fathers; to determine whether gFNP will enhance infant birth status and health status in infancy, breast feeding in the first two months, and immunization take-up during the first year; to identify whether gFNP is cost effective in comparison with routinely available services; and to identify how the program is experienced by women who have a history of being in the care of social services (known as having been ‘looked after’) in comparison with receiving routinely available services.

## Methods/Design

### Study design

The study comprises a multi-site randomized controlled trial in which eligible women are allocated (minimized by site and maternal age group) to one of two arms: i) gFNP delivered via 44 sessions delivered over 76 weeks (N = 100); ii) standard care (N = 100). In addition to the quantitative measures used to compare the two groups qualitative methods will be used to provide a better understanding of the results obtained in the trial.

### Study setting

Sites were included if they responded to an invitation to take part from the FNP National Unit, could demonstrate sufficient women of the relevant age and parity who had given birth in the previous year, and could confirm good links with community midwifery, who also had to sign the expression of interest. Only FNP teams who had delivered the home-based FNP program in its entirety (from birth to child age 24 months) to a cohort of women and with a practising midwife in the team were eligible.

The gFNP program is delivered by two family nurses, one of whom is a practising midwife, in community settings such as Sure Start Children’s Centers, located so that the amount of travelling necessary by group participants is kept to a minimum. Proximity to the location should enhance the rate of attendance and also foster the formulation of social networks. However, so that women from a potentially wider range of home addresses can be recruited to ensure the sample size, funds are available to reimburse intervention participants for travel by public transport to the intervention sessions. Child care is available for any other children. The gFNP program runs from approximately the 16th week of pregnancy to when the babies are 12 months old, meeting weekly or fortnightly during the daytime depending on the stage of the program (14 pregnancy sessions and 30 infancy sessions).

The control group mothers and infants would not be eligible for home-based FNP but will receive all the Universal Core Offer recommended in the Healthy Child Program through midwifery and health visiting services [37]. This is a substantial and universal service for expectant mothers and their infants with a strong evidence base [38] supported by systematic review evidence and NICE guidance. It offers screening tests, immunizations, developmental reviews, information and guidance to support parenting. The latest version has a strong emphasis on pregnancy and the first year of life. Community midwives and health visitors may provide or refer to a range of other community-based or specialist services designed to support young mothers.

Data collection for the study will be conducted by researchers blind to allocation in three visits to participant’s homes (baseline in pregnancy, when infants are two months and twelve months of age), and one telephone contact (when infants are six months old).

### Ethical and research governance approval

The study has been granted ethical approval by the NRES Committee South West-Frenchay (REC reference 13/SW/0086).

### Study timeline

The trial commenced in February 2013 and will be completed in January 2016. Recruitment commenced in July 2013 and takes place in seven sites in England (Barnsley, Dewsbury, Lewisham, Nottingham, Sandwell, South Tyne and Wear and Waltham Forest) through until January 2014. Figure 1 provides details of the timeline for each participant, which will extend from the time that they book in with their midwife (on average at 8 to 12 weeks gestation) through to the end of the study, when their infants are at least 12 months old. The specific time will vary depending on their gestation at booking but will range from 82 to 86 weeks. The intervention arm will receive the gFNP program for 76 weeks on average (from 16 weeks gestation to infant 12 months).

**Figure 1 F1:**
[figure not shown]
Flow chart of participants.

### Randomization

The process will be overseen by the London School of Hygiene and Tropical Medicine Clinical Trials Unit (LSHTM CTU). Identifying information and baseline details of eligible consenting mothers-to-be will be provided by the researchers to the central randomization service at Health Service Research Unit (HSRU), Aberdeen. Minimization criteria will be used to ensure a balance of key prognostic factors using the following two criteria: site and age group (< 20, 20 to 24 years). Allocations to one of two arms will be securely computer generated and delivered by Email to LSHTM. The LSHTM CTU will convey to each gFNP team the names and contact details of women allocated to the intervention arm. The researchers will be blind to allocation.

### Study participants

Women eligible for the trial are expectant mothers prior to 16 weeks gestation with expected delivery dates (EDD) within six to eight weeks of each other for each group in each site, with the range of EDDs specified in relation to the expected date of the first meeting for that site so that the majority would have a gestation of 16 to 20 weeks when the program commences. Specific criteria beyond similar EDDs and gestation were developed based on a formative evaluation [34-36] and on the requirement of the UK FNP National Unit that gFNP should be offered to women not eligible for FNP but be likely to benefit from the content of program, based on research in the USA [11,15]. Thus participants must be either aged < 20 at their last menstrual period (LMP) with one or more previous live births, or aged 20 to 24 at LMP with low educational qualifications and no previous live births. ‘Low educational qualifications’ is defined as not having both Maths and English Language GCSE at grade C or higher or, if they have both of these GCSEs, no more than four GCSEs in total at grade C or higher. Exclusions are: expectant mothers under the age of 20 who have previously received home-based FNP, those in either age group with psychotic mental illness (defined as bi-polar disorder or schizophrenia), or those who are not able to communicate in English since it is not possible to deliver the program in a group context unless all the participants can all understand and speak English.

### Sample size

The sample size was calculated for the two primary outcomes, the revised Adult Adolescent Parenting Inventory (AAPI-2) [39] and the observational CARE Index [40-42]. The standard deviation (SD) of the AAPI-2 is 10, with differences of 6.7 identified in the normative sample between abusive and non-abusive adult females [39]. The standard deviation for the CARE Index is expected to be around 2.3 [41].

For this individually randomized trial, we propose to recruit sufficient mothers and babies (families) to allow the trial to detect a difference between groups of 0.5 standard deviations, with 90% power at a significance level of 0.05 (2-tailed); this is considered to represent a moderate size of effect [43]. Basing calculation on the AAPI-2, very conservatively assuming a correlation of 0.4 between pre and post intervention scores we would need at least 71 families in each arm of the trial to detect this difference. Allowing for an expected 30% drop out rate (based on the first two applications of the program in England) we would need to recruit a minimum of 84 families per arm of the trial. We therefore propose, conservatively, to recruit a minimum of 100 families per arm (N = 200). In the intervention arm this will consist of 10 groups of (generally) 10 families (N = 100), with 2 groups provided per site. However, given that the minimum number required for a viable group is 8, 7 sites are involved in the trial so that it will be possible to recruit a minimum of 208 (if one site proves able to deliver only one group of 8) and potentially at least 224 participants (2 groups of 8 per site plus the same number of controls). It was necessary to have two more sites than the five originally proposed to cope with the possibility that in one or more areas area the minimum number of women would not be recruited to form a viable group. The proposed sample size would similarly allow us to detect a change of approximately 0.5 standard deviations in the CARE index [40-42]. We would therefore expect to be able to detect a difference at follow-up between arms of the trial of approximately 1.2 with 90% power and a 5% level of significance.

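### The recruitment minimum of 84 per arm does not follow from 71 evaluable and 30% dropout (102 does), so the target of 100 per arm carries no margin

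*Protocol article*

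**What the plan says.** The Sample size section sets out to "detect a difference between groups of 0.5 standard deviations", "with 90% power at a significance level of 0.05 (2-tailed"). The calculation is based on the AAPI-2 ("The standard deviation (SD) of the AAPI-2 is 10"), "very conservatively assuming a correlation of 0.4 between pre and post intervention scores". From these inputs it concludes that "we would need at least 71 families in each arm of the trial to detect this difference".

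It then gives an anticipated dropout of 30%, taken from the first two deliveries of the programme in England, and states that "we would need to recruit a minimum of 84 families per arm of the trial". The next sentence builds the target on that figure: "We therefore propose, conservatively, to recruit a minimum of 100 families per arm (N = 200"). The Study design section repeats the same size for each arm, for example "standard care (N = 100").

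Later in the Sample size section, seven sites are said to make a total of at least 208, and potentially 224 or more, possible.

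**The concern.** The inputs and the result stand in consecutive sentences, and the result does not follow from them. Losing 30% of 84 families leaves fewer than 59, although the sentence before asks for at least 71.

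The error matters mainly for how the target is read. Set against a minimum of 84, a target of 100 seems to hold 16 spare families per arm. Set against the correct figure, it holds none. The Recruitment section describes a tight process: at least 16 women per site, with due dates close together, found within six weeks for each delivery. The Sample size section says two sites were added in case some areas could not form a group. If recruitment ended between 84 and 100 per arm, the trial team and its oversight committees would take the text to mean that the power requirement was still met, when at the expected loss it would not be.

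**Working it through.** **Inputs, all from the Sample size section:** difference 0.5 SD; two-sided 5% level (z = 1.96); 90% power (z = 1.2816); baseline–outcome correlation 0.4; dropout 30%.

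**Step 1: reproduce the 71.** With baseline adjustment the variance is multiplied by 1 − 0.4² = 0.84.

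n per arm = 2 × (1.96 + 1.2816)² / 0.5² × 0.84 = 84.06 × 0.84 = 70.6, rounded up to 71. The plan's figure reproduces.

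**Step 2: allow for dropout.** Recruited n = 71 / (1 − 0.30) = 101.4, so 102 per arm or 204 in total. The common shortcut of multiplying by 1.30 gives 92.3, so 93. Neither gives 84. The stated minimum is 102 − 84 = 18 families per arm too low (36 in total).

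**Step 3: what 84 covers.** 1 − 71/84 = 15.5%, about half the stated rate. At 30% loss, 84 × 0.70 = 58.8 remain.

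**Step 4: AAPI-2 power at 30% loss.** Normal approximation: power = Φ(0.5 / √(0.84 × 2/n) − 1.96), with n the evaluable number per arm. For n = 70: 0.5 / √(0.84 × 2/70) = 3.227; 3.227 − 1.96 = 1.267; Φ(1.267) = 89.8%. The last column uses the noncentral t distribution.

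| Recruited per arm | Evaluable per arm | Power, normal | Power, t |
|---|---|---|---|
| 84 (stated minimum) | 58.8 | 84.1% | 83.5% |
| 100 (target) | 70.0 | 89.8% | 89.3% |
| 102 (71/0.70) | 71.4 | 90.3% | 89.9% |
| 104 (208 in total) | 72.8 | 90.8% | 90.5% |
| 112 (224 in total) | 78.4 | 92.7% | 92.4% |

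The normal approximation is the method that yields the plan's 71. By the t-based method 71 evaluable gives 89.8%, so the two columns should not be mixed when a row is compared with 90%.

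**The case against.** **The 84 is not the operative number.** This is fair. The target is at least 100 per arm, seven sites are engaged so that 208 to 224 can be reached, and nothing in the article stops recruitment at 84. At 104 to 112 per arm, power is above 90% by either method. The 208 to 224 is, however, described as possible, while the formal minimum remains 100 per arm. The operational plan lowers the practical risk but does not make the calculation right.

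**A reader might infer that 100 per arm leaves the trial materially underpowered.** The figures do not support that. The gap is one evaluable family per arm (70 against 71), or 0.2 percentage points by the method that produced the 71. That is small beside the uncertainty in any dropout forecast.

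**A reader might also infer that the dropout step was left out**, because the sample size without baseline adjustment is 84.06. The document does not establish this. Under the rounding that turns 70.6 into 71, 84.06 becomes 85. A 15% allowance fits as well: 71/0.85 = 83.5, so 84.

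**The 30% may have been meant for the intervention arm only**, since it comes from experience of the programme, which controls do not receive. It would average 15% over the two arms. With 84 recruited per arm, this would leave 58.8 and 84 evaluable and about 89.4% power (normal approximation). But the text gives one rate without restriction and states the result for each arm. If this was the intention, it needs to be said.

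**Conclusion.** The figure of 84 is wrong on the plan's own inputs; 71 evaluable with 30% loss needs 102 recruited per arm. At 84 per arm, AAPI-2 power would be 83 to 84%. The target of 100 per arm is essentially at the stated power (89 to 90%) but has no margin and is nominally two families per arm short, so calling it conservative is not justified. This is an error in a stated sample-size figure and in the margin inferred from it; it is not a demonstrated power failure of the trial as planned.

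The conclusion assumes that 30% applies equally to both arms and means loss of the 12-month AAPI-2. It takes the plan's effect size and correlation as given and, like the plan's own calculation, makes no allowance for clustering within intervention groups or for having two primary outcomes.

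**What to change.** 1. In the Sample size section, replace 84 with 102 per arm (204 in total). If a different dropout rate was used, state it, say which arm or arms it applies to, and reconcile it with the 30%.
2. Delete *conservatively* from the sentence that sets the target.
3. Then choose one of two statements. Either set the minimum at 102 or more per arm in both the Sample size and Study design sections, and bring the description of ten groups of ten into line (13 groups of 8 give 104 per arm; 14 give 112). Or keep 100 per arm and state that AAPI-2 power is about 89 to 90% at 30% loss.

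The cost is a text correction. The seven-site plan already foresees more than 204 participants, so no site, analysis or design feature has to change.

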### Data management

Quantitative data (summarized in Table 1) will be collected from both the intervention and control arms of the study by study researchers in the participants’ homes and by telephone. The data will comprise a range of self-report questionnaires. Response cards will be used for questions that have a range of possible responses. Home visits will be made at baseline, when participants’ infants are two and twelve months old with a telephone contact when infants are six months old. At 12 months postpartum, data collection will also include independent video-recorded observations of the mother and infant. Researchers will administer questionnaires orally where required with the anticipation that some participants may have low levels of literacy. Researchers will be trained together to ensure that similar methods are used in all locations and the trial manager will accompany them on a percentage of home visits throughout the study to maintain quality.

**Table 1 T1:** Details and timing of data collection

**Measure**	**Baseline, gestation 10 to 14 weeks**	**Infant 2 months, home visit**	**Infant 6 months, telephone interview**	**Infant 12 months, home visit**
Adult-Adolescent Parenting Inventory (AAPI-2)	X			X
CARE index				X
Demographics	X	X (update)	X (update)	X (update)
Edinburgh Postnatal Depression Scale (EPDS)	X	X	X	X
Infant feeding	X (plans)	X	X	
Infant immunizations		X		X
Maternal drug use	X	X (update)		X (update)
Maternal quality of life (EQ-5D 5L)	X	X	X	X
Maternal smoking and alcohol use	X	X (update)		X (update)
Parenting stress index short form (PSI)		X		X
Perceived parenting competence (PSOC)		X		X
Relationship violence	X			X
Social networks (MOS)	X			X
Service use		X	X	X

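### The 90% power stated for the CARE Index relies on a baseline correlation this outcome cannot have; with 70 evaluable per arm, power at 0.5 SD is about 84%

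*Protocol article*

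**What the plan says.** The Sample size section presents one calculation as serving both primary outcomes: "The sample size was calculated for the two primary outcomes, the revised Adult Adolescent Parenting Inventory (AAPI-2) [39] and the observational CARE Index". The target is 0.5 SD with 90% power at two-sided 5%. The number, which is per arm, comes from the AAPI-2: "Basing calculation on the AAPI-2, very conservatively assuming a correlation of 0.4 between pre and post intervention scores we would need at least 71 families". The section expects 30% dropout and proposes at least 100 families per arm (N = 200), the figure also given under Study design. It adds that seven sites could yield 208 to 224 participants.

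The CARE Index is then covered by extension. The section gives its spread ("The standard deviation for the CARE Index is expected to be around 2.3") and continues: "The proposed sample size would similarly allow us to detect a change of approximately 0.5 standard deviations in the CARE index". The conclusion follows: "We would therefore expect to be able to detect a difference at follow-up between arms of the trial of approximately 1.2 with 90% power".

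Three other places bear on this:

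- **Data management:** "At 12 months postpartum, data collection will also include independent video-recorded observations of the mother and infant". Table 1 marks the AAPI-2 at baseline and 12 months, but the CARE Index at 12 months only.
- **Primary outcome measures:** the CARE Index is scored from a three-minute video of mother-child play. Baseline is in pregnancy, so it could not be measured then.
- **Data analysis, Outcomes:** the baseline value of an outcome is fitted as a covariate only where one is available.

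**The concern.** The AAPI-2 figure of 71 is small because adjusting for a baseline score correlated 0.4 with the outcome removes 16% of the variance. The protocol treats the resulting sample size as giving the same power for the CARE Index. That outcome has no pre-intervention score, so there is neither a change to analyse nor a variance reduction to claim.

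The CARE Index is one of two primary outcomes and the only one that is observed and coded blind; the AAPI-2 is self-report. If its power is overstated, a null CARE result will be read as stronger evidence of no effect than the design supports.

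**Working it through.** **Inputs (all from Sample size unless noted).** Effect 0.5 SD; power 90%; two-sided 5%; correlation 0.4 (AAPI-2 only); CARE SD 2.3; CARE difference 1.2 points; dropout 30%; 100 recruited per arm. CARE timing is from Table 1.

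**1. Reproduce the 71.** With a baseline covariate, n per arm = 2 × (1.960 + 1.282)² × (1 − r²) / d².

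- Without the correlation: 2 × 3.2415² / 0.25 = 84.06, so 85 per arm (t-based solution 85.03).
- With r = 0.4: 84.06 × (1 − 0.16) = 70.6, so 71 per arm.

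The stated 71 is therefore an analysis-of-covariance figure. The correlation accounts for the whole reduction from 85 to 71.

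**2. Evaluable number.** 100 × 0.7 = 70 per arm.

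**3. CARE effect in SD units.** 0.5 × 2.3 = 1.15 points, and 1.2 / 2.3 = 0.522 SD. The two CARE sentences therefore describe slightly different effects, and both are checked.

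**4. CARE power without a baseline covariate.** Normal approximation: power = Φ(d × √(n/2) − 1.960). For n = 70 and d = 0.5 this is Φ(2.958 − 1.960) = 84.1%. The table gives this and the noncentral-t result.

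| Evaluable per arm | Power at 0.5 SD: normal / t | Power at 1.2 points: normal / t |
|---|---|---|
| 70 (100 recruited, 30% lost) | 84.1% / 83.6% | 87.0% / 86.5% |
| 71 (the stated requirement) | 84.6% / 84.1% | 87.5% / 87.0% |
| 73 (208 recruited in total, 30% lost) | 85.6% / 85.1% | 88.3% / 87.9% |
| 78 (224 recruited in total, 30% lost) | 87.8% / 87.4% | 90.3% / 89.9% |
| 85 | 90.3% / 90.0% | 92.5% / 92.3% |
| 100 (no loss) | 94.2% / 94.0% | 95.8% / 95.7% |

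**5. Where 90% at 0.5 SD comes from.** Carrying r = 0.4 over to the CARE Index gives 89.8% at 70 per arm and 90.2% at 71 (normal). At the planned evaluable size, 90% at 0.5 SD appears only with the correlation borrowed from the AAPI-2.

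**6. Detectable difference with 90% power at 70 per arm.** Normal: 3.2415 × √(2/70) = 0.548 SD, or 1.26 points. t-based: 0.552 SD, or 0.552 × 2.3 = 1.27 points.

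**7. Numbers needed for 90% power (normal).**

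- For 0.5 SD: 85 evaluable, and 85 / 0.7 = 121.4, so 122 recruited per arm.
- For 1.2 points: 78 evaluable, and 78 / 0.7 = 111.4, so 112 recruited per arm.

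**The case against.** The strongest reply is that the sentence giving 90% refers to about 1.2 points, not 0.5 SD, and that the same section expects seven sites to bring in 208 to 224 women. With 224 recruited and 30% lost (78.4 per arm), unadjusted power at 1.2 points is 90% and the detectable difference is 1.198 points. With 208 it is 1.244 points, which still rounds to 1.2. This arithmetic is right, and against that sentence the gap at N = 200 is about 3 percentage points rather than 6. But the sample size actually proposed is 100 per arm. The larger totals are contingent on recruitment, and the preceding sentence claims 0.5 SD, where even 224 recruits give only about 87% to 88%.

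A second reply is that the inputs are soft. The effect sizes are approximate and the SD is only expected to be around 2.3. At 70 per arm, power for 1.2 points would be 89.3% with an SD of 2.2 and 83.6% with an SD of 2.4. That is a fair caution about precision, but it works in both directions and does not justify using the correlation.

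Third, the 30% comes from earlier deliveries of the programme. The protocol plans to collect outcomes from women who stop attending and describes retention measures. If 85 of 100 per arm were measured, 90% at 0.5 SD would be met. That stands as a qualification, but 30% is the loss the section itself applies, and its power statement should hold under it.

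Finally, the analysis is not mis-specified: baseline values are fitted only where available, and the sentence after the word change refers to a difference at follow-up. The error lies in the power statement alone.

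**Conclusion.** The concern holds. On the protocol's own inputs (100 per arm, 30% lost, SD 2.3, two-sided 5%), CARE Index power is about 84% at 0.5 SD and about 87% at 1.2 points, against a stated 90%. The type II error at 0.5 SD is about 16% rather than 10%. The difference detectable with 90% power is about 1.27 points rather than 1.2.

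The result assumes an unadjusted comparison at 12 months with 70 evaluable per arm. It would be less severe with more recruits or lower loss; the break-even at 0.5 SD is 85 evaluable per arm. No allowance is made for clustering within the intervention groups or for having two primary outcomes; any clustering would lower power further. The error is modest in size, but it is a wrong stated figure for a primary outcome.

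**What to change.** Restate the CARE Index part of the Sample size section without a baseline correlation. For example: with 100 families per arm and 30% loss, the trial has about 84% power to detect a difference of 0.5 SD (1.15 points) in the CARE Index at 12 months, and 90% power for about 1.27 points. Replace the reference to a change with a difference at 12 months. If the larger recruitment is meant to support the claim, say so and give the figures for 208 and 224 alongside.

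Pre-specifying baseline AAPI-2, which is already collected, as a covariate in the CARE model could recover some precision. The protocol gives no correlation between the two measures, so no gain should be built into the stated power. A correlation of 0.4 would be needed to bring power at 0.5 SD back to about 89% to 90% with 70 per arm.

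The correction costs wording only. Sample size, endpoints and data collection stay as they are; the price is a less favourable stated power.
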